### Assessing association with morbidity outcomes

Analyses for morbidity outcomes will be conducted using multivariable generalized linear models (GLMs) with the appropriate link function chosen based on the outcome [67]. To account for potential informative censoring by the competing risk of death, we will use a weighted GLM with inverse probability of censoring weights (IPCW) [68, 69] and will compute robust standard errors. IPCW will be estimated from a logistic regression with the outcome of availability of morbidity information and predictors related to the morbidity and mortality (e.g., patient risk factors). In the weighted GLM, the association between delivery of CRI and morbidity outcomes will be assessed by including and testing the effect of a binary indicator for treatment. The effect of trauma-to-CRI time will be investigated using flexible, potentially non-linear (e.g., sigmoidal, exponential, piecewise) relationships.

For the secondary objective, we will examine the effect of individual resuscitative interventions on morbidity outcomes in treated patients using similar GLMs with intervention and time-to-CRI defined based on the specific treatment. Analysis will be performed in appropriate subgroups (e.g., injury type, injury severity) for injury-specific interventions.

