**Fig. 1 Fig1:**
[figure not shown]
Relative transport distances from EpiC study sites to the tertiary trauma care center (Tygerberg Hospital)

Tygerberg Hospital is the tertiary trauma (referral) center that provides specialty surgical and trauma care to a catchment area of 3.4 million people and attends to over 107,000 admissions annually of which 12,000–15,000 are seriously injured persons [35, 36]. All other EpiC hospital sites (Khayelitsha, Ceres, and Worcester Hospitals) refer complex and critical trauma patients to Tygerberg Hospital for a full range of trauma subspecialty care and consultations [37]. Khayelitsha Hospital is a frontline, district level facility that serves a dense urban catchment area of over 400,000 people and treats around 3,000 patients per month in the Emergency Center, many with injuries from interpersonal violence and motor vehicle collisions [38–40]. Worcester Hospital is a regional level facility that serves a rural population of 917,000 and can provide intensive care and general surgical care. Ceres Hospital is a rural, small district level facility without specialist physicians and offers basic trauma care. Patients at Ceres Hospital who require sub-specialty trauma and surgical care are stabilized and transferred to a trauma center by WCG EMS ambulances.

The WCG EMS is a public prehospital agency that annually treats and transports over 500,000 patients to hospitals, 40% due to trauma [41, 42]. Most ambulances are staffed by basic and intermediate life support providers, whereas advanced life support capable crews are reserved for the most critically injured patients [41, 42]. EpiC will include ambulances servicing catchment areas of the four participating hospitals. The Forensic Pathology Service (FPS) of the Western Cape has a constitutional mandate to perform autopsies on all unnatural deaths, including all trauma deaths. Two FPS labs will participate in this study: the Tygerberg FPS lab (includes deaths of patients from Tygerberg and Khayelitsha Hospital) and the Worcester FPS Lab (includes Worcester and Ceres Hospital deaths) [43].

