2^O^—30-day in-hospital mortality	All-cause mortality at any point during the hospital stay	Time-to-event	Hospital or Pathology
2^O^—Non-resuscitative surgical interventions	Post-injury interventional procedures such as fasciotomies, limb amputation, and laparotomies	Binary	Hospital
2^O^—Secondary infections	Post-injury infections such as wound infections, pneumonia, and sepsis	Binary	Hospital
2^O^—Organ failure	Organ failure will be assessed by individual organ (acute kidney injury, coagulopathy, and acute lung injury) and by a composite multiple organ failure score such the SOFA score up to 7-days	Continuous	Hospital

1^O^ = primary exposure or outcome; 2^O^ = secondary exposure or outcome; Data Source: EMS data is abstracted from WCG EMS Electronic Patient Care Reports, hospital data is abstracted from handwritten medical charts, and pathology data is abstracted from handwritten postmortem/autopsy reports from the Forensic Pathology Service of South Africa. EMS = Emergency Medical Services, ISS = Injury Severity Score, AIS = Abbreviated Injury Scale (anatomical score), SOFA = Sequential Organ Failure Assessment

The primary outcome of mortality will be defined as time to ambulance death or in-hospital death within 7 days of injury. The definition of examining mortality within 7 days was previously selected by a 20-person expert trauma panel to be the ideal duration to assess deaths for a study focused on the effects of early trauma resuscitation [52]. A study of three trauma-focused randomized controlled trials in urban U.S. settings have demonstrated that most hemorrhagic deaths occur in hospitals and within 6 h of patient encounter [51]. However, in our setting we examine a longer window since early deaths are more likely to occur at the scene due to the higher prevalence of penetrating injuries and fewer ambulance resources, and consequently later deaths will likely occur post-EMS transfer and hospital arrival. We will define the secondary outcomes of 24-h and 30-day mortality as time to in-ambulance or in-hospital mortality from injury. Other secondary outcomes include patients’ morbidity and need for operative interventions (those that are not considered damage control surgery), secondary infections (including wound infections, pneumonia, and sepsis), and organ failure (defined with the Sequential Organ Failure Assessment (SOFA) Score [53, 54]).

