### Missing data

Missingness of key measures will be minimized during the data collection process. The primary analysis will be a complete-case analysis that excludes observations that are missing key exposure, outcome, and predictor variables. Characteristics will be compared between those with and without complete data. Sensitivity analyses will be conducted using imputation methods for missing predictor values based on multiple imputation techniques [70].

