### Power calculation

Based on a conservative estimate from the smallest hospital, we assume an average of 3,600 cases from each of the four hospitals in a 4-year period. Thus, we anticipate a total sample size of 14,400 cases over the study period. We assume that 30% of cases have an average trauma-to-CRI time within 2 h of injury and an average 7-day mortality of 10% for the primary mortality outcome. From a Cox proportional hazards regression, with 80% power (alpha = 0.05, two-sided) we can detect a hazard ratio of 0.85 for trauma-to-CRI time within the first 2 h versus not. For the morbidity outcomes, we present the power calculation for a continuous outcome (organ failure), and a binary outcome (wound infection). For the continuous outcome of organ failure, assuming the standard deviation of the SOFA score is 4 [71], with 80% power (alpha = 0.05) we can detect a mean decrease in score of 0.20 in those with trauma-to-CRI time within the first 2 h versus not, which corresponds to a standardized effect size of 0.05. For the binary outcome indicating whether a wound infection occurred, if 10% of cases with a trauma-to-CRI time within 2 h have a wound infection, with 80% power (alpha = 0.05, two-sided) we can detect an odds ratio of 0.84 for trauma-to-CRI time within 2 h versus not.

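### The morbidity weights are introduced to handle death but are modelled on any unavailability of data, so one weight covers both the dead and unscored survivors; the SOFA detectable difference assumes that every case is scored

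*Protocol article*

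**What the plan says.** Under Assessing association with morbidity outcomes, the article plans weighted generalized linear models. The reason given for weighting is that death is a competing event which may censor morbidity informatively. The event modelled is wider: "IPCW will be estimated from a logistic regression with the outcome of availability of morbidity information". The predictors are variables related to morbidity and mortality, with patient risk factors as the example.

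Table 2 takes organ failure from hospital records, by individual organ and by a "composite multiple organ failure score such the SOFA score up to 7-days". The table's footnote says that hospital data are abstracted from handwritten charts. The inclusion criteria admit emergency center walk-ins and set no admission or severity threshold.

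Under Missing data, the primary analysis is a "complete-case analysis that excludes observations that are missing key exposure, outcome, and predictor variables". The imputation planned for sensitivity analyses covers predictors only.

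Under Power calculation, "we anticipate a total sample size of 14,400 cases over the study period", with "30% of cases have an average trauma-to-CRI time within 2 h of injury" and an average 7-day mortality of 10%. For organ failure, "assuming the standard deviation of the SOFA score is 4", the article states: "with 80% power (alpha = 0.05) we can detect a mean decrease in score of 0.20".

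**The concern.** The reason for the weights and the event they model are different. Death is one way for a SOFA score to be unavailable. A survivor may also lack one because components were never recorded, because discharge came early, or because the chart is incomplete. A single availability probability cannot tell these apart, so scored patients are weighted up to represent both those who died and survivors who were never scored.

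The two groups probably lie at opposite ends of the scale. The article describes record abstraction and no study-mandated tests, and one site is described thus: "Ceres Hospital is a rural, small district level facility without specialist physicians and offers basic trauma care". It is reasonable to expect fuller scoring in sicker patients, though the article does not say so. If scoring follows clinical state that the weight model does not contain, availability depends on the outcome itself and the weights cannot fully remove that dependence.

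Two things are at stake. The SOFA contrast may be biased, and its target (survivors or all patients) is left open. The power statement also counts patients whom the weighting section expects to lose.

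**Working it through.** **1. Reproducing the stated 0.20.** Inputs from Power calculation: N = 14,400, split 30/70 (4,320 against 10,080), SD 4, alpha 0.05, power 80%. Sidedness is not given for this outcome; two-sided is used.

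Detectable difference = (1.960 + 0.842) × 4 × √(1/(0.3n) + 1/(0.7n)) = 24.454/√n.

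At n = 14,400: 24.454/120 = 0.204, or 0.051 SD. This rounds to the stated 0.20 and 0.05. Power for exactly 0.20 is 78.5%. A one-sided test would give 0.18, so the figure is two-sided. It reproduces only with a SOFA score for every case.

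**2. Removing only the plan's own deaths.** 10% of 14,400 is 1,440, leaving 12,960. Detectable difference = 24.454/113.84 = 0.215. Standard error = 4 × 2.182/113.84 = 0.0767; 0.20/0.0767 − 1.960 = 0.65, so power for 0.20 is about 74%. This assumes that every death is unscored.

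**3. Range for availability.** The article gives no rate, so these shares are assumptions. SD 4 and the 30/70 split are kept, and precision lost to weighting is ignored.

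| Share scored | n | Detectable difference |
|---|---|---|
| 100% | 14,400 | 0.204 |
| 90% | 12,960 | 0.215 |
| 60% | 8,640 | 0.263 |
| 40% | 5,760 | 0.322 |
| 20% | 2,880 | 0.456 |

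**4. Can the single weight mislead?** This was checked by an illustrative simulation in which every parameter is assumed: 400,000 patients, a measured severity x, a clinical state u outside the weight model, and exposure A with log-odds −0.9 + 0.4x. The underlying state is L = 2 + 2x + 1.5u − 0.5A. The score is L plus unit-variance noise, treated as unbounded. Death has log-odds −4.5 + 0.6L and scoring −1.5 + 0.6L; only scored survivors are analysed. One logistic availability model uses x, x² and A. A second run sets the coefficient of u to zero.

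| | u drives scoring and death | Measured variables only |
|---|---|---|
| Died / alive unscored / scored | 7% / 55% / 38% | 6% / 55% / 39% |
| Mean: all patients | 1.85 | 1.86 |
| Mean: survivors | 1.63 | 1.74 |
| Mean: single weight | 2.35 | 1.70 |
| Effect: all patients | −0.50 | −0.51 |
| Effect: survivors | −0.48 | −0.51 |
| Effect: single weight | −0.41 | −0.49 |

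In the first run the weighted mean lies above both populations and the effect is 0.07 to 0.09 too small in absolute size. In the second run the single weight is nearly right.

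**The case against.** The strongest reply has five parts.

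- **Availability is not documented.** Nothing in the article says that SOFA is recorded mainly in sicker patients. The statistical section describes a cohort at moderate to high baseline risk, and Ceres patients needing sub-specialty care are transferred to a trauma center. This stands: the selection is an inference.
- **The score covers a window.** Up to 7 days is not a day-7 measurement. A patient discharged or dead earlier may already have a score, and individual organ outcomes are listed separately. This stands, so early death or discharge does not automatically mean a missing outcome.
- **Scoring rules may sit elsewhere.** A data dictionary or fuller plan may say how unmeasured components are scored. This is fair, and the absence of that rule is not the point here. The mismatch between the reason for the weights and the event modelled is in the text itself.
- **The predictor list is only an example.** Severity, site or physiology could be added, and inverse-probability weighting of complete cases is a standard method. This stands, and the second simulation run shows that good predictors can make one weight adequate.
- **Scoring the unmeasured as normal could do harm.** If testing follows critical resuscitative interventions or trauma-center care, zeros for untested patients would flatter the untreated. This stands against using that convention alone.

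None of this explains why weights meant for death are fitted to general availability, or why the power figure counts all 14,400.

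**Conclusion.** The point holds as a mismatch within the morbidity section, with a consequence for the power statement. One weight is made to represent the dead and unscored survivors, and the target population is not named. Whether this biases the SOFA contrast depends on whether measured predictors explain both scoring and death. The simulated bias is illustrative and is not an estimate for this study.

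The best-supported figure is the detectable difference. The stated 0.20 needs all 14,400 cases scored, which sits badly with the plan's own 10% mortality and its premise that death censors morbidity. About 0.215 follows if those deaths are unscored; 0.26 to 0.46 rests on assumed availability of 60% down to 20%. All of these are before any loss from weighting.

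Three stronger readings are tempting and not supported. A reader might infer that SOFA can be scored only in patients sick enough to be tested and kept in hospital; the article gives no availability rate. A reader might infer that the endpoint therefore describes no real population; the second simulation run contradicts that as a general statement. A reader might also assume a mean of 5 points in scored patients and near 0 in the others, and set that gap against 0.20 as a 25-fold error. That compares an error in level with a between-group contrast, and an error in level biases the contrast only so far as it differs by exposure.

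Organ failure is a secondary outcome, though it is the continuous one chosen for the power calculation. The change should be made, but the primary mortality analysis does not depend on it.

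**What to change.** **Assessing association with morbidity outcomes.** Replace the single availability model with two components: the probability of surviving to outcome assessment, and the probability of being scored among survivors. Use severity, site and early physiology as predictors in both. State whether the target is survivors or all patients. For survivors, weight by the inverse of the second probability. For all patients, weight by the inverse of the product, and say that this refers to the score had death not intervened. Say whether patients who die after being scored contribute.

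**Unscored survivors.** Present two analyses side by side: one treating unmeasured components, and days after live discharge up to day 7, as normal; and one restricted to measured components. The normal-value convention hides unrecognised dysfunction, and the amount hidden may differ by intervention or site, so it should not stand alone.

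**Power calculation.** Restate the detectable SOFA difference for the number expected to be scored, and allow for the loss of precision from weighting. The pilot phase, which assessed missing data, may supply an availability rate.

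**Cost.** Analysis wording, one additional weight model and one additional SOFA analysis. No new data are needed.

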### Missing data

Missingness of key measures will be minimized during the data collection process. The primary analysis will be a complete-case analysis that excludes observations that are missing key exposure, outcome, and predictor variables. Characteristics will be compared between those with and without complete data. Sensitivity analyses will be conducted using imputation methods for missing predictor values based on multiple imputation techniques [70].

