### Inclusion and exclusion criteria

The EpiC study will include adult patients aged 18 years and older with a clinical encounter for a traumatic injury at one or more of our 10 study sites. Eligible patients will meet one of the following criteria: (1) arrive and/or depart by WCG EMS to/from a participating site, (2) transported via WCG EMS with initial signs of life or receive prehospital resuscitation care, but die in the ambulance prior to hospital arrival, (3) were alive at the time of the EMS call but were deceased upon their arrival, or (4) emergency center walk-ins. Those under the age of 18 years, prisoners, injury onset > 24-h prior to arrival at first study site, bites, stings, other forms of envenomation, toxicologic injuries, drownings, patients who are found deceased on scene, and/or patients transported via private EMS (non-WCG EMS) will be excluded.

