### Variables, outcomes, and study measures

Epidemiologic information will be collected for each study participant for their entire clinical course at all associated study sites, including: patient demographic information (e.g., age, sex, race, and comorbidities); injury details (e.g., time, type, and intent); facility data (e.g., hospital name, trauma level, clinician qualifications, units of care); clinical data (e.g., vital signs, medications administered, critical interventions, operations performed); and, trauma system process (e.g., key dates and times [51]). Table 2 describes the exposures, predictors, and outcomes of interest in the EpiC study.

**Table 2 Tab2:** Key EpiC Study Exposure, Predictors, and Outcome Measures

Exposures	Definition	Variable Type	Data Source
1^O—^Critical resuscitative interventions (CRI)	Prehospital and in-hospital resuscitative interventions or therapeutics, delivered for the patient’s traumatic injury (e.g., thoracostomy for tension pneumothorax), within the first 24 h post-injury	Binary	EMS and/or Hospital
1^O^—Trauma-to-CRI time	Duration of time from injury to receiving a critical resuscitative intervention for the dominant injury	Continuous	EMS, Hospital, and/or Pathology

Predictors	Definition	Variable Type	Data Source
Age	Span of years lived at the time of injury	Continuous	EMS, Hospital, or Pathology
Sex	Biological sex given at birth	Categorical	EMS, Hospital, or Pathology
Comorbidities	One or more pre-existing disease or conditions present in the patient that are trauma-relevant chronic conditions (e.g., bleeding disorder)	Binary	EMS or Hospital
Socioeconomic status	Based on hospital insurance status	Categorical	Hospital
Mechanism of injury	Main force that created the injury or how injury was inflicted (e.g., firearm, Struck/hit, stabbing or cut, vehicular injury, fall, thermal, choking/hanging, iatrogenic, other)	Categorical	EMS, Hospital, or Pathology
Provider level	Health care provider qualifications (e.g., rank of EMS provider, type of doctor)	Categorical	EMS
Injury severity	ISS calculated as the sum of squares of 3 worst AIS scores. Low (< 12) or high (≥ 12)	Continuous, Binary	EMS, Hospital, or Pathology

Outcomes	Definition	Variable Type	Data Source
1^O—^Ambulance death or 7-day in-hospital mortality	All-cause mortality in the ambulance or within the hospital in the first 7-days post-injury	Time-to-event	EMS, Hospital, or Pathology

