## Statistical methods

Descriptive statistics will be estimated for all demographic, injury, facility, clinical, and systems process fields. Multivariable models will adjust for characteristics at the patient-level (e.g., age, sex, race, comorbidities, socio-economic status, injury mechanism, injury severity index) and provider-level (e.g., specialist trauma surgeon, general medical officer, advanced prehospital provider), as described in Table 2. Due to the small number of hospitals, site will be adjusted for as a fixed effect.

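### The primary complete-case mortality model adjusts for a covariate recorded only in hospital, so as written it would be expected to drop ambulance deaths, a named part of the primary outcome

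*Protocol article*

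**What the plan says.** All references are to the protocol article.

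- **Missing data.** "The primary analysis will be a complete-case analysis that excludes observations that are missing key exposure, outcome, and predictor variables". Imputation is secondary: "Sensitivity analyses will be conducted using imputation methods for missing predictor values based on multiple imputation techniques".
- **Statistical methods.** The patient-level adjustment variables are given as "age, sex, race, comorbidities, socio-economic status, injury mechanism, injury severity index", with a pointer to Table 2.
- **Table 2, socioeconomic status.** The definition is "Based on hospital insurance status" and the only source is Hospital. The table's footnote adds that "hospital data is abstracted from handwritten medical charts". By contrast, age, sex, mechanism and severity may come from EMS, hospital or pathology records, and comorbidities from EMS or hospital records.
- **Inclusion and exclusion criteria.** Criterion 2 enrols WCG EMS patients who "die in the ambulance prior to hospital arrival".
- **Table 2, primary outcome.** "All-cause mortality in the ambulance or within the hospital in the first 7-days post-injury".
- **Table 2, provider level.** The definition runs "Health care provider qualifications (e.g., rank of EMS provider, type of doctor", yet the only source listed is EMS.

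**The concern.** Each of these statements is ordinary alone; together they conflict. A patient who dies before reaching hospital would not be expected to have an insurance status in a hospital chart. A Cox model cannot use a record that lacks one of its covariates, and the complete-case rule makes exclusion the stated primary approach. The article gives no exemption for ambulance deaths, no second source for socioeconomic status and no category for an unknown value.

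The missingness would then be created by the outcome itself, at its earliest and most severe end. The analysed endpoint would drift towards in-hospital death only, while the reported endpoint still names ambulance death. The article does not appear to intend this. The section on mortality outcomes presents the method as following people who were alive when help was first requested. The Limitations section names only deaths during non-EMS transport as not captured, which implies that deaths during EMS transport are meant to stay in.

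**Working it through.** **1. Reproduce the plan's figure.** Inputs from Power calculation: 14,400 cases, 10% 7-day mortality (1,440 deaths), 30% with CRI within 2 h, hazard ratio (HR) 0.85, 80% power, two-sided alpha 0.05.

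Events needed (Schoenfeld) = (1.960 + 0.842)² / [0.3 × 0.7 × (ln 0.85)²] = 7.849 / (0.21 × 0.02641) ≈ 1,416. Expected: 1,440.

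Power = Φ(√(1,440 × 0.21) × 0.1625 − 1.960) = Φ(0.866) = 0.807.

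The stated figure reproduces. It counts every death, and no allowance for incomplete cases is stated.

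**2. Power if ambulance deaths are lost.** The ambulance share of deaths, s, is not given, so it is assumed here. The same formula is used with 1,440 × (1 − s) events.

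| s (assumed) | Deaths left | Power |
|---|---|---|
| 1% | 1,426 | 0.803 |
| 5% | 1,368 | 0.787 |
| 10% | 1,296 | 0.765 |
| 20% | 1,152 | 0.715 |

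**3. Crude illustration of bias.** Take 4,320 early-CRI and 10,080 other patients, 1,440 deaths, and a true risk ratio of 0.85.

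Risk in others = 1,440 / (10,080 + 0.85 × 4,320) = 1,440 / 13,752 = 10.47%, or 1,055.5 deaths. Risk in early CRI = 0.85 × 10.47% = 8.90%, or 384.5 deaths.

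Now delete 144 ambulance deaths (s = 10%). Let x be the assumed share of them with early CRI.

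- x = 0: others (1,055.5 − 144) / (10,080 − 144) = 911.5 / 9,936 = 9.17%. Ratio 8.90 / 9.17 = 0.97.
- x = 30%: early (384.5 − 43.2) / (4,320 − 43.2) = 341.3 / 4,276.8 = 7.98%; others (1,055.5 − 100.8) / (10,080 − 100.8) = 954.7 / 9,979.2 = 9.57%. Ratio 0.83.

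The same calculation over a range of assumptions:

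| s (assumed) | x = 0 | x = 15% | x = 30% |
|---|---|---|---|
| 1% | 0.86 | 0.85 | 0.85 |
| 5% | 0.91 | 0.87 | 0.84 |
| 10% | 0.97 | 0.90 | 0.83 |
| 20% | 1.14 | 0.97 | 0.81 |

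The ratio stays at 0.85 when x is about 26%. Below that the apparent benefit shrinks; above it, the benefit is exaggerated.

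These are fixed-group risk ratios. The planned model is a Cox regression with time-dependent CRI, so the table shows that the deletion can matter and in which directions. It does not predict the primary estimate.

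**The case against.** Several counterarguments have weight.

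- **The word *key* is not defined in the Missing data section, and coding may be left to an analysis plan that is not shown.** This is fair as far as it goes. However, the article itself names socioeconomic status as a model covariate, gives it a single source and fixes complete-case as primary. The conflict lies in what is stated.
- **No passage says that ambulance deaths have no hospital record.** That is true, and it is why the point is worded as an expectation. The same uncertainty applies to patients found dead on arrival.
- **Multiple imputation of predictors is already planned.** It is only a sensitivity analysis. If no ambulance death has an observed insurance status, imputation would also extrapolate wholly from patients who reached hospital.
- **The direction of bias is open.** A reader might infer that the lost deaths are mostly untreated, so that deletion works against the study hypothesis. The article does say that CRI in the ambulance is limited, but this describes the whole cohort. Criterion 2 admits some ambulance deaths because they received prehospital resuscitation, and Table 2 counts prehospital interventions as CRI. Either direction is possible.
- **The ambulance share may be small.** The article expects early deaths at the scene and later ones after hospital arrival, which lends no support to a large share. At 1% the effect is slight.

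A reader might also infer from the EMS-only source for provider level that walk-ins are to be deleted. The document does not support that as the intention: the definition mentions doctors, and Statistical methods lists surgeons and medical officers as provider levels. The source cell looks incomplete.

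**Conclusion.** The point stands as a structural conflict. Followed as written, the primary analysis would be expected to exclude ambulance deaths that its own outcome definition includes. This rests on one inference: that patients who never reach hospital have no hospital insurance status on record.

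The consequence cannot be sized from the document. With 10% of deaths in the ambulance (assumed), a true ratio of 0.85 could appear as anything from about 0.97 (none with early CRI) to 0.83 (30% with early CRI), on a crude scale that is not the planned estimator. Power would drop from 0.81 to about 0.79 or 0.76 if 5% or 10% of deaths were lost. The bias matters more than the power loss, because the deletion depends on the outcome. A claim of bias in one particular direction, or of a large effect, is not supported. The power calculation is correct on its own inputs.

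**What to change.** 1. Leave hospital insurance status out of the primary mortality model. Restrict its covariates to those that EMS, hospital or pathology records can supply for every care pathway. Make the same check for race and site, which are in the model but not listed in Table 2.
2. State that no patient with a known primary outcome is excluded for a covariate that cannot be recorded on that patient's care pathway.
3. Report the model with insurance status as a sensitivity analysis among patients who reached hospital.
4. Correct the Table 2 source for provider level to EMS or Hospital, in line with its own definition and with Statistical methods, so that walk-ins without an EMS record are not dropped by a literal reading.

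A separate category for no hospital encounter is not a good substitute: for ambulance deaths, membership is determined by dying, so the covariate would absorb part of the outcome. Making imputation of insurance status the primary approach is also weak, for the extrapolation reason given above.

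The cost is a change of wording and modest programming, with no new data. The one loss is adjustment for insurance status in the primary model, which the sensitivity analysis partly restores.
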